**Fig. 2 Fig2:**
[figure not shown]
Multidisplicinary digital therapeutic app ‘MORA Cure PFP’ based on self-guided personalized exercise therapy and cognitive behavioral therapy for patellofemoral pain

For participants in the control group, a healthcare professional with experience in musculoskeletal disease treatment will conduct self-exercise education according to the paper-based self-guided exercise material. The exercise education will last for at least 15 min, and participants will be instructed to record the time spent on self-exercise in the patient diaries distributed at baseline. At each subsequent visit, participants will be asked to bring their ongoing diaries, and whenever feasible, the diaries will be collected to monitor their progress.

### Strategies to improve adherence to interventions {11c}

To enhance adherence, participants are provided with education on the importance of treatment after group allocation. The experimental group receives instructions on using the application, while the control group is taught self-exercise using dedicated materials.

Each participant is required to perform daily self-treatment and log their activities, including exercise completion and duration. For the experimental group, the application automatically tracks and records exercise times, ensuring consistent monitoring. In the control group, participants manually log their exercise in a paper diary. During each visit, the investigator collects the diaries and monitors progress, offering support and feedback to encourage continued adherence.

### Participant timeline {13}

Participants in this clinical trial will complete 4 to 5 outpatient visits: V1 (Screening), V2 (Baseline), V3 (In-treatment), V4 (Post-treatment), and V5 (Follow-up). V2 must occur within 4 weeks of V1 and may be conducted on the same day as V1. V3 is scheduled 4 weeks after V2, with an allowable range of 3 to 5 weeks. V4 is set for 8 weeks after V2, with a window of 8 to 9 weeks, and V5 is scheduled 12 weeks after V2, with an allowable range of 12 to 13 weeks. See Table 2 for the specific schedule of assessments for each visit. For Visit 3, participants may not need to visit the medical institution in person. In this case, certain checks, such as prior medication, concomitant medication, and adverse event assessments, may be omitted. Pain intensity assessment and the Kujala evaluation will be conducted by sending a survey link to the participant, who will complete it while in contact with the clinical trial site representative over the phone.

**Table 2 Tab2:** Assessment schedule by visit

Schedule	Screening (V1)	Baseline (V2)^1^	In-treatment (V3)^2,3^	Post-treatment (V4)^4^	Follow-up (V5)^5^
	− 4 weeks ~ 0 week	0 week	3 weeks ~ 5 weeks	8 weeks ~ 9 weeks	12 weeks ~ 13 weeks
Informed consent	X				
Screening number assignment	X				
Demographics	X				
Medical history	X				
Height and weight measurement		X			
Physical examination	X	X	X^3^	X	X
Concomitant/previous medication history	X	X	X^3^	X	X
Knee X-ray Imaging and K-L grading	X^6^				
Inclusion/exclusion criteria review	X	X			
Selection of target knee (L/R)		X			
Randomization and assignment of registration number		X			
Pain intensity assessment		X	X	X	X
Kujala questionnaire		X	X	X	X
EQ-5D-5L questionnaire		X		X	X
PHQ-9 questionnaire		X		X	X
PCS questionnaire		X		X	X
Overall perceived recovery score assessment				X	X
Disease education		X			
Investigational device prescription and app installation (treatment group only)		X			
Education on self-exercise (control group only)		X			
Self-exercise patient diary distribution (control group only)		X			
Self-exercise patient diary return (control group only)			X^7^	X^7^	X
Adverse event review		X	X^3^	X	X
Investigational device app deletion (treatment gropu only)					X

1. V2 must be conducted within 4 weeks of V1, and V1 and V2 can take place on the same day

2. V3 is conducted 4 weeks after V2, with a permissible variation of one week before or after (3 to 5 weeks)

3. For V3, a visit to the medical institution may not be required. In this case, previous and concomitant medication reviews, as well as adverse event reviews, may be omitted. Pain intensity and Kujala assessments can be remotely collected by sending a link through a phone call

4. V4 is conducted 8 weeks after V2, with a permissible delay of one week (8 to 9 weeks)

5. V5 is conducted 12 weeks after V2, with a permissible delay of one week (12 to 13 weeks)

6. If an X-ray taken within 3 months is available for K-L grade evaluation, this may be omitted

7. For V3 and V4, the self-exercise log should be reviewed, and completed logs should be collected

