### Composition of the data monitoring committee, its role and reporting structure {21a}

This study does not include a data monitoring committee (DMC). The decision to exclude a DMC is based on the fact that the study involves minimal risk to participants, and the investigational medical device has already demonstrated a favorable safety profile in prior studies. Additionally, the study design allows for close monitoring by the investigators and sponsor through regular site visits and data reviews, ensuring that participant safety and data integrity are adequately maintained without the need for an independent monitoring committee.

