### Adverse event reporting and harms {22}

All adverse events that occur or worsen after obtaining the subject’s consent will be collected, except for those who fail the screening. Pre-existing signs or symptoms at the time of consent are recorded in the medical history section of the CRF. AEs should be monitored until symptoms resolve and the condition stabilizes, and progress reports may be required by the sponsor. The investigator should provide a clear diagnosis, or otherwise record symptoms/signs. Appropriate examinations and treatments must be administered for all AEs. If an AE makes it difficult to continue the trial, the subject may drop out or the trial may be discontinued, with the best treatment provided for safety.

The CRF must record whether the AE is treatment-emergent (TEAE), the onset and end dates, severity, causal relationship with the investigational device, actions taken, and outcome. Serious adverse events (SAEs), serious adverse device effects, and unexpected adverse device effects must be reported to the IRB and regulatory authorities within the required timeframes. Specific AEs, such as worsening knee pain, cramps, dizziness, changes in mood or thought patterns, and any other significant AEs, must be documented and shared with the sponsor within 24 h.

All adverse events that occur will be standardized using System Organ Class (SOC) and Preferred Term (PT) with the latest version of MedDRA. Treatment emergent adverse events (TEAEs) that occur after application of the investigational medical device will be counted as one event when the same SOC and PT adverse event occurs multiple times in one subject, and when the severity differs for the same adverse event, it will be handled with the maximum severity. When the causal relationship differs for the same TEAE in one subject, it will be handled in the direction of higher relatedness to the investigational medical device. Summary and analysis of adverse events will be performed for TEAEs. The number of subjects experiencing events, incidence rates, and number of events will be presented for TEAEs, knee-related TEAEs, ADEs, and SAEs.

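### A remote V3 may skip the adverse-event and medication reviews although site staff are on the phone, so 8 to 9 weeks, the whole treatment period, can pass without a scheduled review

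*Protocol article*

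**What the plan says.** Participant timeline {13} allows V3 to take place without attendance at the site. In that case "certain checks, such as prior medication, concomitant medication, and adverse event assessments, may be omitted". Note 3 to Table 2 gives the same permission for the medication and adverse-event reviews, so it is not a slip of wording in one place. The article states no condition or limit on when V3 may be remote.

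The same paragraph says that the pain and Kujala survey is sent as a link to the participant, "who will complete it while in contact with the clinical trial site representative over the phone". A member of site staff is thus in live contact with the participant at the moment when the reviews may be left out.

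The Table 2 row reads "Adverse event review X X^3^ X X": the review is scheduled at V2, V3, V4 and V5, and the V3 entry carries note 3.

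Three other places bear on this:

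- Adverse event reporting and harms {22} sets out to collect all adverse events from consent onward. It names some (worsening knee pain, cramps, dizziness, changes in mood or thinking) that "must be documented and shared with the sponsor within 24 h".
- The data monitoring committee section {21a} explains the absence of a committee partly on the ground that "the study design allows for close monitoring by the investigators and sponsor", by means of site visits and data reviews. It also cites minimal risk and the safety profile in prior studies.
- Statistical methods {20a} tests differences between the arms in the percentages with treatment-emergent adverse events (TEAEs).

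**The concern.** V3 is the only scheduled visit between the start of treatment and week 8. The permission removes the one planned occasion in mid-treatment on which participants are asked about adverse events and about other medication or treatment. Being remote does not explain the omission, because both reviews are questions and someone is on the line to ask them. Of the items marked with note 3 in Table 2, only the physical examination needs the participant to be present.

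The stake is the quality of the safety data. Without a V3 question, an event in the early weeks enters the record only if the participant volunteers it or recalls it at V4. The same holds for prohibited treatments, which are grounds for withdrawal under the discontinuation criteria {11b}. PHQ-9 is not scheduled at V3 either. After an omitted review, the only outcome assessments in Table 2 between V2 and V4 are pain and knee function. Neither is a question about cramps, dizziness or mood, which {22} singles out in a trial of an app that includes cognitive behavioral therapy.

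How completely events are found would also depend on whether V3 was in person or remote. That matters more in an open-label trial that compares TEAE percentages between arms.

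**Working it through.** **Inputs**, all from Participant timeline {13} and Table 2:

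- V2 is week 0. Under the intervention description {11a}, the app programme starts on the day it is set up after prescription at baseline, and it runs for 8 weeks.
- V3: "V3 is scheduled 4 weeks after V2, with an allowable range of 3 to 5 weeks".
- V4: "V4 is set for 8 weeks after V2, with a window of 8 to 9 weeks".
- V5: "V5 is scheduled 12 weeks after V2, with an allowable range of 12 to 13 weeks".

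**Formula.** Interval between two scheduled reviews = week of the later visit minus week of the earlier visit. The shortest and longest values come from the ends of the windows.

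**With a review at V3**

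- V2 to V3: 3 − 0 = 3 weeks to 5 − 0 = 5 weeks.
- V3 to V4: 8 − 5 = 3 weeks to 9 − 3 = 6 weeks.
- Longest interval for one participant up to V4: at best 4 weeks (V3 at week 4, V4 at week 8) and at worst 6 weeks (V3 at week 3, V4 at week 9).

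**With the V3 review omitted**

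- V2 to V4: 8 − 0 = 8 weeks to 9 − 0 = 9 weeks.

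**After V4, the same in both cases**

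- V4 to V5: 12 − 9 = 3 weeks to 13 − 8 = 5 weeks.

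| | First review after baseline | Longest interval between reviews, V2 to V4 |
|---|---|---|
| Review done at V3 | week 3 to 5 | 4 to 6 weeks |
| Review omitted at V3 | week 8 to 9 | 8 to 9 weeks |

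The programme lasts 8 weeks and V4 cannot fall before week 8. With the V3 review omitted, the first scheduled review after baseline therefore comes no earlier than the end of the programme.

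**Passages side by side.** {22} wants every adverse event after consent, while {13} waives the only scheduled enquiry during treatment for participants seen remotely. {21a} leans on close monitoring, while {13} thins out what there is to monitor: site visits and data reviews can only check what has been asked and recorded. These passages pull in different directions, but each can be followed without breaking the other.

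**The case against.** The other side has several sound points.

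- **No contradiction with {21a} or {22}.** A reader might infer that the permission contradicts the reason for having no committee and the 24-hour rule. It does not. The monitoring in {21a} works through site visits and data reviews, which a remote V3 leaves in place, and {21a} gives further reasons. The 24-hour rule sets how fast a listed event goes to the sponsor, not how often participants are asked. Tension is the right word.
- **Not a gap without any check.** Usual pain, worst pain and Kujala are still collected at a remote V3, and under {18b} the investigator checks treatment progress at each visit. Worsening knee pain may show in those scores. What is missing is the adverse-event and medication review.
- **Safeguards remain.** Events can be volunteered on the call or recalled at V4. Under {11b} the investigator must try to contact anyone who misses a visit and confirm their well-being, and withdrawn participants stay in the safety evaluation. TEAEs count once per participant and term, so an event recalled at V4 still counts.
- **No headcount can be given.** A reader might apply the 20% dropout allowance to the sample, 0.20 × 216 = 43.2, and infer that about 43 participants might never be asked. The documents give neither dropout timing nor the share of remote V3 visits. Anyone who leaves before V3 would go unasked even with a V3 review.
- **Per-protocol set.** A reader might infer that membership turns on visit mode. Members must complete the trial, so they still meet the medication reviews at V4 and V5. At most, detection is later and relies on recall.
- **Arm imbalance.** Nothing in the documents says that remote V3 will be more common in one arm.
- **Condensed article.** Call scripts may sit in the full protocol. That would answer a complaint about missing detail, but this is a permission stated twice.

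These points limit the consequences. None of them gives a reason to skip two questions on a call that already takes place.

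**Conclusion.** The point stands as a weakness in safety ascertainment. If a site uses the permission, the longest interval between scheduled adverse-event and medication reviews rises from at most 6 weeks to 8 to 9 weeks and covers the whole treatment period. The likely effect is that some TEAEs and some use of prohibited treatment are recorded late or not at all, to a degree that depends on visit mode. A biased comparison of TEAE percentages would further require remote V3 to be used, or reviews to be skipped, unequally between arms. That is possible in an open-label trial but not shown.

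The interval assumes that visits keep to their windows. How many participants are affected cannot be estimated, because omission is optional, applies only to a remote V3, and no rate of remote visits is given. No effect on the primary endpoint or the sample size is claimed. The change is worth making because it is cheap.

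**What to change.** In Participant timeline {13} and note 3 to Table 2, delete the permission to omit the medication and adverse-event reviews. State instead that the standard adverse-event question and the concomitant medication/treatment question are asked at every V3 contact, in person or by phone, and entered in the eCRF. Only the physical examination is dropped when V3 is remote.

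The cost is a few minutes per call and an edit in two places. No visit, outcome or sample size changes.

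Trial status gives recruitment as running from April 2024 to the end of December 2024. If V3 visits have already taken place under the present rule, report by arm how many were remote and in how many the reviews were done, so that readers can judge the TEAE comparison.

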### Outcomes {12}

The primary efficacy outcome of this trial is usual pain intensity score (VAS, 100 scale) at 8 weeks (V4). For secondary outcomes, see Table 1. For the method of aggregation, all outcome measures will be analyzed as continuous variables using mean values with appropriate statistical comparisons between groups (For further detail, see Statistical Analysis).

Through interviews, demographic information, medical history, surgical history, and prior/concomitant medications will be collected. Physical examination will include measurements of height, weight, and a patella examination. A knee X-ray will be taken to assign a K-L grade [40], which is used to assess exclusion criteria for osteoarthritis.

The usual and worst pain intensity scores assess the average and peak knee pain experienced over the past week, respectively. Participants mark their pain level on a visual analog scale from 0 to 100, with values recorded and rounded to the nearest whole number [41].

To assess knee function, participants complete the anterior knee pain scale (Kujala score), 13-item self-report questionnaire [42], with a total score calculated from the responses. Quality of life is assessed via the EQ-5D-5L [43] questionnaire, recording the sum of scores across five questions and today’s health status score. Depression severity is evaluated using the Patient Health Questionnaire-9 (PHQ-9) [44], with a total score from nine questions, while pain catastrophizing is assessed using the Pain Catastrophizing Scale (PCS) [45], totaling scores from 13 questions. Participants also rate their perceived recovery level on a 0 to 6 scale [46].

All pain and questionnaire assessments are conducted as electronic patient-reported outcomes (ePRO). Participants use digital tools provided at the site, with data automatically transferred to the electronic case report form (eCRF). For visit 3, if conducted as a televisit, participants may complete the assessments remotely.

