## Assignment of interventions: blinding

### Who will be blinded {17a}

This clinical trial is open-label; therefore, blinding is not applicable.

Due to the nature of digital healthcare apps, complete blinding of participants and investigators is not feasible. Statistical analysis by the biostatistician will commence only after trial completion and proper verification of all data followed by database lock. (For further detail, See “Data management {19}”). The additional benefit of blinding the biostatistician is limited.

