### Methods in analysis to handle protocol non-adherence and any statistical methods to handle missing data {20c}

For the analysis of the FAS, missing values occurring after treatment that are used for primary and secondary efficacy evaluation variables will be imputed using the last observation carried forward (LOCF) method. However, when imputing missing values, results prior to the administration of the investigational medical device will not be substituted for post-administration results. Other data will be analyzed as collected (available data) without imputation.

For the analysis of the PPS, missing values will not be imputed and will be analyzed as collected.

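### At a remote V3 the pain and Kujala link is completed during a call with unmasked site staff, leaving avoidable room for staff influence on the week-4 endpoints (minor)

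*Protocol article*

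**What the plan says.** The Participant timeline section of the protocol article makes attendance at V3 optional: "For Visit 3, participants may not need to visit the medical institution in person". In that case the pain and Kujala assessments are done through a survey link sent to the participant, "who will complete it while in contact with the clinical trial site representative over the phone".

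Two other places describe the same procedure more loosely. Note 3 to Table 2 reads "Pain intensity and Kujala assessments can be remotely collected by sending a link through a phone call", which does not say that anyone stays on the line while the answers are entered. The Outcomes section says "For visit 3, if conducted as a televisit, participants may complete the assessments remotely" and does not mention a call. It also says that all pain and questionnaire data are electronic patient-reported outcomes, normally entered on digital tools at the site.

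On masking, the section on who will be blinded states "This clinical trial is open-label; therefore, blinding is not applicable", and adds that "complete blinding of participants and investigators is not feasible".

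On missing data in the full analysis set (FAS), post-treatment values for the primary and secondary efficacy variables "will be imputed using the last observation carried forward (LOCF) method". Results from before use of the device may not be carried forward.

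**The concern.** Self-rated pain and function can be affected by who is present when the rating is made. Here the person on the phone belongs to the site team, can know the arm, and works in a trial where visits are also used to give support and feedback on adherence. No stated purpose requires that person to be on the line while the answers are entered, because the link itself delivers the questionnaire. In a trial that cannot be masked, staff influence on answers is one of the few sources of bias that procedure alone can reduce.

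Six secondary endpoints are directly exposed: usual pain, worst pain and Kujala at week 4 (Table 1, items 16-18) and their changes from baseline (items 33-35). Table 1 labels the visit for items 16-18 as V2, but the schedule places week 4 at V3, and they are read that way here. The change scores may also mix modes, since baseline is collected under the on-site rule and V3 may be remote.

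The primary endpoint is at V4. It is exposed only where V4 is missing and a V3 score is carried into its place.

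**Working it through.** **Passages side by side.** The Participant timeline text has staff in contact during completion. Note 3 to Table 2 has a call that delivers the link. The Outcomes section has remote completion with no call. A site could follow any of the three and believe it was compliant.

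**The plan's own figure.** With d = 0.428, two-sided alpha 0.05 and power 0.80, n = 2 × (1.960 + 0.842)² / 0.428² = 85.7, so 86 per group. Then 86 / (1 − 0.2) = 107.5, so 108 per group and 216 in total. The stated sample size reproduces.

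**Inputs for the illustration.**
- From the Sample size section: 108 per arm, 20% dropout (cited range 10-30%), and exploratory-trial SDs of 1.49 and 2.43. The pooled SD is √((1.49² + 2.43²)/2) = 2.016, about 20.2 if that scale is multiplied by 10 to match the 0-100 VAS.
- Assumed: SD 20, baseline correlation 0.5, the share of V3 visits held remotely, and the between-arm reporting difference b caused by the call. The documents give none of these last three.

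**Standard error of an adjusted contrast.** SE = 20 × √(1 − 0.5²) × √(2/108) = 2.36 points.

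**Week-4 contrast.** Shift = b × remote share. Two-sided error = Φ(−1.96 − shift/SE) + 1 − Φ(1.96 − shift/SE).

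| Assumption | Shift | Shift/SE | Error |
|---|---|---|---|
| b = 3, half remote | 1.5 | 0.64 | about 10% |
| b = 5, half remote | 2.5 | 1.06 | about 18.5% |
| Call moves both arms by 5; 70% v 30% remote | 0.4 × 5 = 2.0 | 0.85 | about 14% |

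Without baseline adjustment (SD 20.2, SE = 20.2 × √(2/108) = 2.74), the second row becomes 14.9%.

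**Week-8 primary through carry-forward.** The shift is further multiplied by the share carried forward. Take 20%, and assume that every dropout has a V3 score:
- 1.5 × 0.2 = 0.3 points: error about 5.2%
- 2.5 × 0.2 = 0.5 points: error about 5.5%
- 2.0 × 0.2 = 0.4 points: error about 5.3%

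The exploratory-trial difference behind the sample size is 3.18 − 2.31 = 0.87, about 8.7 points on the 0-100 scale under the same rescaling. The 0.5-point shift is about 6% of that (0.5/8.7).

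**Range for the primary.** Using SD 20.2 unadjusted, with b from 2 to 10, 25-100% remote and 10-30% carried forward, the shift runs from 0.05 to 3.0 points and the error from 5.0% to 19.4%. The top figure needs all three inputs at their maximum.

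**Whether carry-forward reaches the primary at all.** The FAS definition requires post-randomization primary efficacy data. If that means a V4 value, no primary value is ever imputed and the effect is nil. The FAS definition and the missing-data section leave this unclear. The per-protocol set is not imputed in either case.

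**The case against.** The best defence is that little is added to the bias already inherent in an open-label design. An on-site V3 also takes place among unmasked staff, the call is the same procedure in both arms, and participants know their own arm. The scores are self-entered, and no passage says that answers are spoken, read out or seen. The Limitations section already concedes subjective measures and the lack of blinding. The call may also do useful work, by getting the link completed within the V3 window and keeping the rating on the target knee. Because baseline cannot be carried forward, a lost V3 score matters.

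Most of this stands as a limit on size. It shows that the increment over site presence is unknown and that removing the contact would leave participants' own knowledge of their arm untouched. It does not explain why staff need to be on the line while the answers are entered, and the wording still differs between places.

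Two stronger readings are tempting:
- **That the V3 mode is chosen after allocation and so differs by arm.** V3 falls after randomisation, and diary review gives control participants more reason to attend, whereas app use is logged automatically. But the documents do not say when, by whom or at what level the mode is chosen, and the full protocol may. The 70%/30% row above is therefore only a what-if.
- **That the primary test is materially inflated.** The 10%, 14% and 18.5% figures are undiluted week-4 values and should not be read across to week 8.

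**Conclusion.** The point holds in a narrow form and is minor. The article states a procedure that puts an unmasked site representative in contact with the participant during self-rating at a remote V3, and describes the same step differently in the note to Table 2. This leaves avoidable room for staff influence on six of the 35 secondary endpoints.

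The effect on the primary is small under moderate assumptions: about 0.5 points and 5.5% error with a 5-point differential, half of V3 visits remote and 20% carried forward. It is nil if the FAS requires a V4 value. These figures rest on an assumed SD, baseline correlation, remote share and differential. The documents give no evidence that a bias exists or how large it would be.

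**What to change.** Reconcile the Participant timeline text with note 3 to Table 2. Both should say that the call serves for reminders, confirming the target knee and technical help, and that the participant enters and submits the answers alone, with staff not reading, hearing or discussing them.

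Record V3 mode (remote or on-site) for each participant if this is not already captured, tabulate it by arm, and add a sensitivity check of the week-4 results by mode. Recruitment began in April 2024, so some V3 data may already exist; for these, mode can be tabulated as far as site records allow.

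The cost is a sentence in each of two places, a line of site training and one data field. The downside is slightly more follow-up for late submissions and possibly a small rise in missing V3 scores, which keeping the call as a reminder should limit. The sample size is unchanged.
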